The majority of phones used in LMIC are feature phones (non-smart), which are not compatible with the technologies that have been demonstrated to enhance TB care in developed countries [25]. In LMICs, the evidence for the impact of MHIs on TB treatment outcomes is limited to studies involving short message service (SMS) interventions. Although SMS interventions seem to be generally associated with higher treatment success [26], the results from LMICs have been contradictory. Some studies have reported a significant impact on treatment success [12] while others did not find better treatment outcomes with SMS interventions [27–29]*.* The implementation of SMS MHIs is low in LMICs because of high illiteracy and preference for voice-based communication [30–32]*.* Interactive voice response technology (IVRT) delivers voice calls that do not require reading skills. Therefore, IVRT may be acceptable and may have a greater impact. While there is increasing evidence for use of IVRT to optimize care in people receiving HIV care and other health services [33–35], no study has evaluated the impact of mobile-based IVRT on TB treatment outcomes in Africa. We used the information, motivation, and behavioral skills (IMB) model of behavioral change [36] to guide the design of an IVRT-based technology that enhances adherence to TB treatment. The IMB model was initially developed to modify HIV-risky behaviors and has now been adopted to guide behavioral change in developed countries [34]. The model suggests that the motivation of TB patients, increasing adherence skills, and providing information on TB treatment would improve adherence. The model was used to target increase adherence and retention in care since improving these aspects may increase treatment success (Fig. 1).

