### Trial endpoints

The primary endpoint is treatment success (at 6 months): treatment success is a composite outcome, comprising treatment completion and cure in patients with clinically and bacteriologically diagnosed TB, respectively. It is a robust and agreed indicator of treatment success in TB programs. In patients with bacteriologically diagnosed TB, cure is defined as having a negative sputum test in the last month of treatment and on at least one previous occasion [47]. For clinically diagnosed patients, completion entails 6 months of therapy. The denominator for each arm will be the number of patients enrolled. At the same time, the numerator is the sum of bacteriologically and clinically diagnosed patients with cure or treatment completion, respectively.

This RCT also has several secondary endpoints. First, we will determine the TB cure rates in patients with microbiologically diagnosed TB. Second, we will determine treatment completion for patients clinically diagnosed with TB in the two arms: Third, retention rates will be determined and compared between the study arms. Patients will be deemed to be actively engaged in care if they attend a clinic visit within one month of a scheduled appointment. Additionally, we will compare appointments. We will categorize visits as “early,” if they present before an appointment, “prompt” if they show up within three days after the appointment date, “late” if they present after three days but within 30 days of a scheduled appointment and missed if patients do not show up at all or present after 30 days. Fourth, we will determine the incremental costs per additional DALY averted per percentage point increase in treatment success in the intervention versus the control arm. In addition, we will compare adherence rates at months 2 and 6. Depending on the availability of drug susceptibility tests, we will compare the rates of MDR-TB. To understand the impact of the intervention on the treatment outcomes and the potential for adoption and scaling of the intervention, we will explore the perceptions and experiences of patients and care providers towards the MHI. Finally, we will determine the uptake and adherence to the intervention. We will consider the successful receipt of a reminder as a proxy for the utilization of the technology. Therefore, we will determine the proportion of successful calls in the intervention and control arms.

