### Sample size determination

Based on results from a randomized controlled trial in Kenya that demonstrated a 9% increase in TB treatment success following the use of SMS [12], we hypothesize that the interactive voice response platform will lead to at least a 6% higher impact as compared to SMS reminder treatment success (i.e., a 15%-point difference compared to the control arm). A retrospective cross-sectional study of routine data on HIV/TB co-infected patients from the Uganda National Tuberculosis and Leprosy Program reported lost to follow-up rates of 3.5% and 16.6% in urban and rural settings, respectively [7]. The rate of lost-to-follow at the three TB clinics was approximately 11.8%. Therefore, assuming an 11.8% lost-to-follow-up rate, this study would require a minimum of 274 (137 patients per arm) patients to demonstrate a 15% increment in treatment success with a power of 0.8 and precision of 0.05.

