### Analysis of endpoints

The planned analyses are summarized in Table 2. We will use a two-tailed *p* value of 0.05 and report the 95% confidence intervals for all endpoints. In all analyses, we will control for confounders of adherence and retention [7, 48, 49]. In both primary and secondary outcomes, we will undertake per-protocol and intention-to-treat analyses.

**Table 2 Tab2:** Analysis of quantitative outcomes

Outcomes	Measure of outcomes (intervention versus control arm)	Statistical analysis
Treatment success	Proportion of patients with treatment success at six months. Odds ratio of treatment success	Logistic regression, odds ratios
Cure rates	Proportion of patients cured of TB; odds ratio of TB cure	Logistic regression, odds ratios
Treatment completion	Treatment completion rate; odds ratio of treatment completion	Logistic regression, odds ratios
Retention in care	Hazards of attrition in the intervention versus control; Cumulative attrition at six months	Cox’s proportional hazards model, log-rank test
Adherence to TB medicines	Mean adherence rates (proportion of TB medicines)	Mann-Whitney U test and Poisson regression
Appointment keeping and punctuality	Proportion of patients who keep an appointment; Proportion of patients with early, prompt, and late visits	Ordered logistic regression
Drug-resistant TB rates	Proportion of patients with rifampicin-resistant TB	Logistic regression, odds ratios
Call success rates (2,4, and 6 months)	Proportion of successful calls	*t* test

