### Analysis of the primary endpoint

We will use logistic regression to determine the crude and adjusted odds ratios of treatment success in the intervention arm versus the control arm. The multivariable model will adjust just for potential confounders, including age, sex, employment status, bacterial load at baseline, TB category, and HIV status [7, 48, 49]. The stepwise backward elimination method will be used to fit the final model. The model with the lowest Akaike information criterion (AIC) statistic will be considered the best fitting. Covariates with a global/trend *p* value > 0.2 at the bivariate analysis, will be adjusted for in the final multivariate model. We will explore factor interactions, including the interaction between age adherence and sputum smear results at baseline. Where interaction is confirmed, we report both the main and interaction effects.

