### Analysis of quantitative endpoints

Logistic regression will be used to determine the adjusted odds ratio for TB cure and treatment completion in the intervention arm versus control arms. We will also determine the predictors of TB cure overall and in both arms. The final model will adjust for age, sex, bacterial load, HIV status, TB site, and symptoms at baseline. We will also determine and compare attrition in the two study arms using the Cox proportional hazards model. We will compute the crude and adjusted hazard rates of attrition in the intervention and control arms. The log-rank test will be used to test for differences in attrition between the study arms. Tests for the Cox proportional hazard assumption will be done graphically using Schoenfeld residuals. The model will adjust for age, sex, Karnofsky score at baseline, HIV status, transport costs, distance from the health facility, TB site, and socioeconomic covariates.

We will compare the mean adherence rates (proportion of TB medicines taken as evidenced by TB card) at 6 months in the intervention and control arms. We will treat adherence as a continuous covariate and compare the median adherence between the intervention and control arms. To compare appointment keeping, we will use ordinal logistic regression to determine the adjusted odds ratios of missed, late, and prompt visits (early used as a reference group). In the sensitivity analysis, Poisson regression will be used to compare the number of missed visits and treatment doses in the intervention and control arms. The models will adjust for age, sex, employment, distance from the health facility, and HIV status. We will use chi-square to compare the proportions of patients with MDR-TB between the two study arms. Additionally, logistic regression will be used to determine the crude and adjusted odds ratios of MDR-TB in the intervention and control arms. Finally, as a proxy for the uptake of intervention and fidelity, we will determine the proportions of successful and dropped and received calls at three different (2, 4, and 6 months) to determine patient exposure and acceptance of the intervention through the study treatment period.

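### The primary-endpoint analysis names adherence, measured after randomisation and on the intended causal path, in an interaction to be explored; the arm odds ratio from such a model is not the total effect of CFL-TB

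*Protocol article*

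**What the plan says.** The section Analysis of the primary endpoint plans crude and adjusted odds ratios of treatment success by arm. The covariates it lists are age, sex, employment status, baseline bacterial load, TB category and HIV status. All are patient or disease characteristics, and adherence is not among them. The section then adds: "We will explore factor interactions, including the interaction between age adherence and sputum smear results at baseline". It continues: "Where interaction is confirmed, we report both the main and interaction effects".

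Other sections show what adherence is in this trial:

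- Introduction, on the behavioural model behind the intervention: "The model was used to target increase adherence and retention in care since improving these aspects may increase treatment success".
- Analysis of quantitative endpoints: "We will compare the mean adherence rates (proportion of TB medicines taken as evidenced by TB card) at 6 months". Trial endpoints also has adherence compared at months 2 and 6, as a secondary endpoint.
- Trial endpoints, on the primary outcome: "For clinically diagnosed patients, completion entails 6 months of therapy".

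**The concern.** The primary objective asks whether allocation to CFL-TB raises treatment success. That is a total effect, including whatever the intervention achieves by improving adherence. Adherence is recorded after randomisation and is a pathway the intervention targets. Conditioning on it removes that part of the effect from the arm coefficient, which then addresses a different question: the effect that does not pass through measured adherence.

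Two further problems follow.

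- Unmeasured causes shared by adherence and success would bias the conditional odds ratio, so randomisation no longer protects it.
- For clinically diagnosed patients, the share of medicines taken comes close to restating the outcome, which is completion of six months of therapy.

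If CFL-TB works as its framework supposes, the arm odds ratio from such a model could sit near 1 despite a real benefit. That figure could then be reported under the primary endpoint.

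**Working it through.** **1. Which models the sentence allows.** The wording is garbled where age and adherence meet. It could mean age × adherence, adherence × smear, a three-way term, or an interaction with arm. Each reading needs adherence as a term in the treatment-success model. If the interaction is with arm, the arm main effect refers to adherence of zero unless adherence is centred.

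**2. The plan's sample size.** Inputs from the article: two-sided 0.05 ("We will use a two-tailed *p* value of 0.05 and report the 95% confidence intervals for all endpoints"), "a 15%-point difference compared to the control arm", 11.8% loss to follow-up, and "274 (137 patients per arm) patients to demonstrate a 15% increment in treatment success with a power of 0.8 and precision of 0.05". The control success rate is not given, so 70% is assumed, with a range of 65% to 75%.

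n per arm = [1.960·√(2·p̄·q̄) + 0.842·√(p₁q₁ + p₂q₂)]² / 0.15², with p₁ = 0.70, p₂ = 0.85, p̄ = 0.775

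= [1.960·√0.34875 + 0.842·√0.3375]² / 0.0225 = 120.5

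120.5 / (1 − 0.118) = 136.6, so 137 per arm and 274 in total. This matches the plan, but other assumed settings also come close (for example 73% versus 88% with a continuity correction), so 70% remains an assumption.

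**3. Power without adherence.** The denominator is all patients enrolled, so 137 per arm is used.

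z = (0.15·√137 − 1.960·√0.34875) / √0.3375 = 1.03, giving power 0.848.

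**4. Power with adherence in the model.** Logistic simulation, 137 per arm, 1,000 replicates per setting. Adherence is a continuous variable in SD units, with log-odds of success 1.0 per SD, and the total effect is calibrated to 70% versus 85%. The share through adherence sets how far the arm shifts adherence; the rest is a direct arm effect. Reliability 0.5 means that half the within-arm variance of measured adherence is noise. The entries are power for the arm coefficient; the crude analysis in the same runs gave 0.84 to 0.88.

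| Share through adherence | Adherence × smear model, measured without error | Arm × adherence model, measured without error | Adherence × smear model, reliability 0.5 |
|---|---|---|---|
| 0% | 0.89 | 0.83 | 0.87 |
| 25% | 0.69 | 0.64 | 0.78 |
| 40% | 0.47 | 0.45 | 0.69 |
| 50% | 0.35 | 0.35 | 0.63 |
| 60% | 0.24 | 0.24 | 0.59 |
| 75% | 0.12 | 0.13 | 0.49 |
| 100% | 0.03 | 0.03 | 0.34 |

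**5. Sensitivity.** With slopes of 0.8 and 1.5 per SD, and success of 65% versus 80%, 70% versus 85% or 75% versus 90%, power in the adherence-interaction model is 0.32 to 0.43 at half mediation, 0.10 to 0.15 at three quarters and 0.02 to 0.03 at full mediation. A second simulation, with both age × adherence and smear × adherence terms, gave 0.43 to 0.48 at half and 0.02 to 0.03 at full mediation (70% versus 85%). The combined range at half mediation for 70% versus 85% is therefore quoted as 0.35 to 0.48.

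**6. Control check.** A model with age, smear and age × smear but no adherence keeps power at about 0.83 to 0.88 (70% versus 85%). The loss comes from adherence, not from fitting an interaction.

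**The case against.** The strongest reply is that the primary estimate is already defined without adherence. The section plans a crude odds ratio and one adjusted for listed covariates that exclude it. The interaction step is described as exploratory and conditional. The outcomes table lists only logistic regression and odds ratios for treatment success. This stands: those two odds ratios keep their meaning and their power.

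A reader might therefore go too far in inferring that the trial loses most of its power. The article does not say that an interaction model replaces the planned odds ratios. It gives no threshold for confirming an interaction and no rule for switching models. If such a rule is imposed (two interactions tested at 0.05, and the arm term taken from the interaction model when either is significant), overall power falls by only about 3 to 8 points when no true interaction exists. It falls to between 0.15 and 0.63 only under an assumed smear-by-adherence difference of 1.0 log-odds per SD, for which the article gives no basis. The share of the effect through adherence is also not stated, retention is named as a second route, and adherence read from a TB card may be measured poorly.

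The objection does not remove the point. The section does not say which odds ratio governs if an interaction is confirmed. Its rule of preferring the model with the lowest AIC does not exclude models containing adherence, which should predict success strongly. Nor is this a detail left to another document: the sentence is present and names an unsuitable variable.

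**Conclusion.** The point holds in a limited form. The article places a post-randomisation mediator in an interaction to be explored for the primary endpoint and commits to reporting the resulting main effects if the interaction is confirmed. The arm odds ratio from any such model is not the total effect of allocation and should not be read as a randomised comparison.

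The effect on power is conditional. More than half of the power of about 0.85 is lost in that model only if adherence is well measured and carries roughly 45% to 50% or more of the effect, or is poorly measured and carries nearly all of it. With reliability 0.5, power is 0.63 at half and 0.34 at full mediation. These figures rest on the assumed control rate, mediation share, adherence slope and measurement quality. The point that the estimand changes needs none of those values; it needs only that adherence lies on the causal path, as the article intends. The correction should be made because it prevents a mediator-conditioned result from being presented for the primary endpoint.

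**What to change.** In Analysis of the primary endpoint, remove adherence from the interactions explored and correct the garbled sentence. State that only baseline variables may enter the primary-endpoint model, including any model compared by AIC, and that the primary arm odds ratio always comes from the model without interaction terms. Interactions between arm and baseline factors, such as age or the baseline sputum result, may be kept as optional exploratory analyses. If the role of adherence is of interest, report it in a separate exploratory mediation analysis, with its assumptions stated.

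The cost is a short change of wording. It needs no new data, visits or patients.

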### Analysis of quantitative endpoints

Logistic regression will be used to determine the adjusted odds ratio for TB cure and treatment completion in the intervention arm versus control arms. We will also determine the predictors of TB cure overall and in both arms. The final model will adjust for age, sex, bacterial load, HIV status, TB site, and symptoms at baseline. We will also determine and compare attrition in the two study arms using the Cox proportional hazards model. We will compute the crude and adjusted hazard rates of attrition in the intervention and control arms. The log-rank test will be used to test for differences in attrition between the study arms. Tests for the Cox proportional hazard assumption will be done graphically using Schoenfeld residuals. The model will adjust for age, sex, Karnofsky score at baseline, HIV status, transport costs, distance from the health facility, TB site, and socioeconomic covariates.

We will compare the mean adherence rates (proportion of TB medicines taken as evidenced by TB card) at 6 months in the intervention and control arms. We will treat adherence as a continuous covariate and compare the median adherence between the intervention and control arms. To compare appointment keeping, we will use ordinal logistic regression to determine the adjusted odds ratios of missed, late, and prompt visits (early used as a reference group). In the sensitivity analysis, Poisson regression will be used to compare the number of missed visits and treatment doses in the intervention and control arms. The models will adjust for age, sex, employment, distance from the health facility, and HIV status. We will use chi-square to compare the proportions of patients with MDR-TB between the two study arms. Additionally, logistic regression will be used to determine the crude and adjusted odds ratios of MDR-TB in the intervention and control arms. Finally, as a proxy for the uptake of intervention and fidelity, we will determine the proportions of successful and dropped and received calls at three different (2, 4, and 6 months) to determine patient exposure and acceptance of the intervention through the study treatment period.

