### Control arm and the standard of TB care in Uganda

The standard of care at all TB treatment centers follows the national TB treatment guidelines [40]. The standard treatment duration is 6 months, except for patients with TB meningitis and osteoarticular TB who require 12 months of treatment. The standard regimen and duration of treatment for patients with drug-susceptible TB are 2 months for isoniazid, ethambutol, rifampicin, and pyrazinamide, followed by four months of rifampicin and isoniazid [34]. Patients are reviewed every 2 weeks for the first month and monthly thereafter. All patients are encouraged to register a close household or community member to directly observe therapy, but this is not enforced. Patients receive health education during clinic visits with messaging on adherence and treatment completion. At treatment initiation, patients are routinely encouraged to adhere to treatment and appointments, but there are often no patient support systems provided to enhance this. Some patients may use other reminder systems of their choice [41] but this has not been described in patients with TB.

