### The intervention (CFL-TB)

CFL-TB delivers once-daily adherence reminders, pre-appointment reminders, and targeted educative behavior change messages and allows patients to report symptoms to health care workers (HCWs) remotely. As advised by Iribarren et al., participants will decide their preferred language and the timing and frequency of reminders and will ensure that the content is culturally sensitive [44]. The software also delivers calls to registered care providers (buddies) of patients to facilitate daily observed therapy (DOTS), in line with the World Health Organization and Ministry of Health guidelines [14, 40]*.* In Uganda, daily reminders are generally preferred by patients over weekly reminders [8]. To increase adherence to the intervention, if the first call is not answered, the system will make two additional calls, 15 min apart. The study staff will also interview participants in the intervention arm to determine whether they are experiencing any problems. Health care workers enroll patients in the system, monitor the delivery message delivery of messages, and provide ongoing technical support, such as setting personal identification numbers (PINs) and swapping the registered telephone numbers. In contrast, participants are responsible for making and receiving calls. We will synchronize appointment reminders with scheduled appointments, and the software will initiate a call before and on the day of the clinic review. Participants select their preferred time to receive the reminder calls and set their PIN. The system offers short educational messages to increase knowledge about TB/HIV and general health [40]. The CFL-TB software is interoperable with other health information systems used in Uganda, including DHIS2, a web-based database for health reporting.

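### Appointment keeping: the ordinal model cannot give the category odds ratios planned, its scale ranks early beyond prompt, and the unit of analysis is contradictory

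*Protocol article*

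**What the plan says.** **Model.** Under Analysis of quantitative endpoints: "we will use ordinal logistic regression to determine the adjusted odds ratios of missed, late, and prompt visits (early used as a reference group"). Table 2 (Analysis of endpoints) also names ordered logistic regression. A Poisson regression on the number of missed visits is planned as a sensitivity analysis.

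**Categories.** Trial endpoints classifies visits. A visit is early "if they present before an appointment" and prompt "if they show up within three days after the appointment date". The remaining two categories, first late and then missed, are worded as follows: "if they present after three days but within 30 days of a scheduled appointment and missed if patients do not show up at all". Attendance after 30 days also counts as missed.

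**Unit.** Trial endpoints and the model sentence speak of visits. Table 2 gives the measure per patient: "Proportion of patients who keep an appointment; Proportion of patients with early, prompt, and late visits".

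**Repeated appointments.** In the section on standard care, "Patients are reviewed every 2 weeks for the first month and monthly thereafter". Participant follow-up sets study evaluations at baseline and months 2, 5 and 6.

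**Reminders.** In the section on the intervention, "the software will initiate a call before and on the day of the clinic review".

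**The concern.** There are three problems, all in the stated text.

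1. **Model and estimate do not match.** A proportional-odds model summarises the arm effect in one odds ratio, common to every cut of the scale. It has no outcome reference category. Odds ratios for missed, late and prompt, each against early, belong to a multinomial model. An analyst cannot do both parts of the sentence.

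2. **The scale penalises a harmless shift.** Taking the categories in the order given, with early at the end opposite missed, a visit that moves from early to prompt counts as a worsening. Nothing in the article says that early attendance is preferable to prompt attendance.

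3. **The unit is not settled.** A patient has several appointments and can be early at one, late at another and absent from a third. The article gives no rule that turns these into one category per patient, yet Table 2 counts patients while the text counts visits.

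Adherence to clinic appointments is a named secondary objective, and appointment reminders are a core part of the intervention. The common odds ratio could understate a real gain in punctuality or, in some circumstances, point the wrong way.

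**Working it through.** The article states no figure for this endpoint, so there is none to reproduce. The sample size of 274 is for treatment success and does not bear on this point. All category rates and intraclass correlations (ICCs) below are assumptions.

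**Effect of the ordering**

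Assumed control arm: early 30%, prompt 45%, late 17%, missed 8%. Assumed benefit: late and missed each fall by 30%, to 11.9% and 5.6%, so late plus missed falls from 25% to 17.5%. Early plus prompt is then 82.5% in the intervention arm, and only the split between the two is varied.

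The model pools three cumulative odds ratios toward worse:
- missed versus the rest: (0.056/0.944)/(0.08/0.92) = 0.68
- late or missed versus early or prompt: (0.175/0.825)/(0.25/0.75) = 0.64
- not early versus early: depends only on the early share. At 30% it is 1.00. At 15% it is (0.85/0.15)/(0.70/0.30) = 2.43.

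The first two show the benefit and do not change. The third carries the early/prompt shift into the pooled result. Fitted common odds ratios:

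| Early, intervention arm | Not-early cut | Common OR toward worse | OR with early and prompt merged |
|---|---|---|---|
| 36% | 0.76 | 0.71 | 0.64 |
| 30% | 1.00 | 0.83 | 0.64 |
| 25% | 1.29 | 0.95 | 0.64 |
| 23% | 1.43 | 1.00 | 0.64 |
| 20% | 1.71 | 1.09 | 0.64 |
| 15% | 2.43 | 1.25 | 0.64 |

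The effect is diluted in every row. The sign changes once early attendance falls below about 23%, a relative fall of (30 − 23)/30, or about a quarter.

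A second set of assumed rates shows the same pattern, with odds ratios now toward better. Control is missed 10%, late 15%, prompt 45%, early 30%, and late plus missed falls from 25% to 15%. The common odds ratio is 1.29 with early unchanged, 0.98 with early at 20% and 0.85 with early at 15%. Merged, it is 1.88 to 1.91.

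**If the visit is the unit and patient is ignored**

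Design effect = 1 + (m − 1) × ICC. Actual two-sided type I error = 2 × [1 − Φ(1.96/√design effect)]. The number of visits m is 3 from the study evaluations (months 2, 5 and 6), or about 7 from the clinic schedule (weeks 2 and 4, then months 2 to 6).

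| m | ICC | Design effect | Type I error |
|---|---|---|---|
| 3 | 0.1 | 1.2 | 0.07 |
| 3 | 0.2 | 1.4 | 0.10 |
| 3 | 0.3 | 1.6 | 0.12 |
| 7 | 0.1 | 1.6 | 0.12 |
| 7 | 0.2 | 2.2 | 0.19 |
| 7 | 0.3 | 2.8 | 0.24 |

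A simulation of 4,000 trials per setting, with 137 patients per arm and the score test of the ordinal model, gave 0.07 to 0.12 for 3 visits and 0.11 to 0.23 for 7. A patient-clustered variance brought these back to 0.04 to 0.05. With one outcome per patient there is no inflation.

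**The case against.** **A reader might infer that repeated visits are treated as independent, so the confidence intervals will be too narrow.** The article does not support this. It nowhere says that each visit is a row or that visits are independent, and Table 2 words the measure per patient. It is a condensed account of a full protocol that is not shown, and the variance method may sit there or in an analysis plan. What stands is the conflict between visits and patients. The inflation is conditional on pooling visits without allowing for patient. Seven visits is also not established, because the study evaluations give only three.

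**A reader might also infer that the reminders will make a benefit look like harm.** That too goes beyond the text. One call comes before the appointment and could raise early attendance just as well as move it toward the day. Reversal needs early attendance to fall by about a quarter in the assumed scenario. Short of that, the direction is right and the effect is understated.

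**Safeguards exist.** The Poisson analysis does not depend on how early and prompt are ordered, and the proportions in Table 2 would help to show a change in attendance. But the Poisson model is a sensitivity analysis and ignores late visits, and descriptive proportions do not correct a misleading odds ratio.

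**Early and prompt are deliberately separate.** That is fair, and a multinomial model would respect it. It is no reason to rank one above the other.

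**Conclusion.** The point holds in this form. The planned sentence asks an ordered model for odds ratios that it cannot give; this needs no assumption. Reading early as the end of the scale opposite missed, the common odds ratio understates a fall in late and missed visits across the range examined: 0.71 to 0.83 where early attendance holds or rises, against 0.64 with early and prompt merged. It reaches about 1.0 when early falls to about 23%, and 1.25 at 15%. These sizes rest on assumed category rates, while the mechanism does not.

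The unit of analysis is contradictory as written. Any excess type I error (0.07 to 0.12 with 3 visits, 0.12 to 0.24 with 7, for assumed ICCs of 0.1 to 0.3) follows only if visits are pooled without allowing for patient.

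The consequence is limited to one secondary endpoint, but a change of wording removes it.

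**What to change.** - Delete the parenthesis that makes early the reference group.
- Merge early and prompt into one category, kept on time. Analyse on time / late / missed by ordinal logistic regression, or on time versus not as a binary outcome, and report early visits descriptively. If the early/prompt distinction is wanted as an estimate, use a multinomial model instead and change the model named in Table 2 to match.
- State one unit of analysis, the same in Analysis of quantitative endpoints and in Table 2. If it is the patient, give the rule that reduces several appointments to one outcome. If it is the visit, use patient-clustered standard errors, GEE or a patient random intercept.

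The cost is analysis wording only, with no new data. Intervals may be wider if visits are the unit, and the early/prompt contrast becomes descriptive unless the multinomial model is chosen.
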